
#### Lifestyle measurements

A short screening questionnaire assessing sleep, physical activity, food consumption/habits, sleep, and screen time is used to differentiate a poor lifestyle from a normal lifestyle. All Lifestyle measures are assessed at T0 (Baseline), T1 (end of intervention), T2 (six months after baseline), T3 (12 months after baseline), except for the shuttle run test (not at T2 (six months after baseline)).I. Lifestyle parameter sleep: sleeping habitsThe Children’s sleep habit questionnaire (CSHQ) is a 33-item parent-report developed for children aged 4–10 [34], and has been used in youth ranging from 2–16 years old [35, 36]. Parents are asked to recall sleep behaviors occurring over a “typical” recent week [34–36]. Items are rated on a three-point scale: “usually” if the sleep behavior occurred five or more times/week; “sometimes” for two to four times/week; and “rarely” for zero to one [34–36]. There are eight scales: Bedtime resistance, Sleep onset delay, Sleep duration, Sleep anxiety, Night wakings, Parasomnias, Sleep-disordered breathing, and Daytime sleepiness [34–36]. The CSHQ can differentiate youth with sleep disorders from those without in typically developing and clinical populations [34, 37, 38]. A cutoff score of 44 is recommended for the 33-item version, where a higher score indicates a sleep disorder [39]. The Dutch CSHQ is the translated version of the American version. The reliability of the CSHQ seems to be adequate and the internal consistency is moderate [40].J. Lifestyle parameter sleep: sleep diaryParents are asked to fill in a visual sleep-wake diary to monitor the child’s sleeping habits and subjective sleep experience (regularity, total bedtime, total sleep time (TST), sleep onset latency (SOL), wake after sleep onset (WASO) and sleep efficiency (SE)).K. Lifestyle parameter Sleep: 24 h sleep/wake measurements and physical activityWith actigraphy, a reliable non-invasive manner to monitor objective sleep parameters, the following parameters were collected: TST, SOL, WASO and SE [41] (http://www.actigraphcorp.com/products/wactisleep-bt-monitor/). Next to these sleep parameters, physical activity (ranging from sedentary behavior to light physical activity to moderate-to-vigorous intensity physical activity) and sedentary bouts (number of daily bouts of sedentary time lasting 1–4 minutes, 5–9 minutes, 10–14 minutes, 15–29 minutes, and 30+ minutes) are objectively and non-invasively measured as well. This way, children’s activity information can be measured in a natural setting for a continuous period. Children are asked to wear a wrist actigraph for a whole week.L. Lifestyle parameter Diet: Food consumptionThe child’s food consumption is measured through an online tool (‘Eetmeter’, Dutch Nutrition Centre) available at both the website of the Dutch Nutrition Centre and as a mobile app (free of charge). All products found in Dutch supermarkets are included in this application, including the standard quantities in which they are eaten. Users can enter all food consumed per main meal (breakfast, lunch, and dinner) and between-main meals (snacks). Parents are asked to track the child's food consumption for two weekdays and one weekend day.M. Lifestyle parameter diet: eating habitsIn addition to the food diary, the child’s eating habits are examined using sections B and C of the Primary Caregivers Questionnaire (PCQ) [42–44]. Parents are asked to complete 77 items assessing their child’s drinking and snacking behavior, including their attitude towards this.N. Lifestyle parameter physical activity: physical fitnessChildren’s physical fitness is measured using the 20-meter shuttle run test [45]. The 20-meter shuttle run test is valid for measuring cardiorespiratory fitness [46].O. Lifestyle parameter physical activity: physical activity questionnaireFurthermore, parents are asked to fill in a questionnaire, including questions about physical activity. Section D of the PCQ [42–44] is used to assess the physical activity behavior of the child. A total of 61 items assess their child's physical activity behavior in the past seven days, including their own attitude towards this.P. Lifestyle parameter screen time: screen activitiesParents are asked to fill in a questionnaire on the screen activities of the child. Section E (sedentary behavior) of the PCQ [42–44] is used to assess the screen-viewing activities of the child. A total of 24 items assess their child’s screen time use and the amount of time spent on the screen, including their own attitude against this. Parents complete items assessing the screen viewing behavior of their child and themselves, including their own attitude towards this.

#### Measurements of costs

Q. Used healthcare resourcesTo examine the healthcare resources used by families and productivity losses (e.g., absence from work of parents) as a consequence of the child’s psychiatric disorder, the ‘Trimbos and iMTA questionnaire on Costs associated with Psychiatric illness’ (Tic-P questionnaire) [47] is used. The number of all healthcare contacts with a 3-month recall period is registered at T3 (12 months after baseline). With this data, the cost-effectiveness of the lifestyle intervention compared to CAU is calculated.

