The primary objective of the Movementss study is to quantify the short-term (after 12 weeks) and long-term (after 6 and 12 months) effectiveness on quality of life compared to care as usual (CAU) in children aged 6–12 years with MI. We hypothesize that the lifestyle intervention will be more effective than CAU. The second aim is to examine the short- and long-term effects of the lifestyle intervention compared to CAU on outcome measures related to mental and physical symptoms and lifestyle problems such as emotional and behavioral problems, cognitive outcomes, sleeping, eating patterns, and weight status. It is hypothesized that lifestyle improvement will have a positive effect on these mental and physical symptoms. Additionally, the third aim is to investigate the cost-effectiveness of the lifestyle intervention compared with CAU. We assume that intervening in lifestyle at such a young age will result in less expensive care in the long term. Also, this study aims to identify potential moderators of adherence or responders to the treatment (e.g., SES, ethnicity, comorbidity). Finally, qualitative questions will be addressed in this study by examining the potential facilitators and barriers to the lifestyle intervention.

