Parallel to these sessions on location, the family will receive visits from the homecoach. The order of the sessions is the guideline for the intervention, however, a certain degree of flexibility is required and accepted in order to make the intervention fit to the family

*CBT* Cognitive Behavioral Therapy, *PMST* Psychomotor Systematic Therapy

^a^The Beweegrichtlijn 2017 advises children (4–18 years) to exercise moderately for at least an hour a day. Longer, more frequent, and/or more intensive exercise provides additional health benefits. Furthermore, children are advised to do muscle and bone-strengthening activities at least three times per week and to avoid a sedentary lifestyle

This intervention will be given by trained mental health professionals (i.e., psychologists and nursing specialists). Prior to the start of the intervention, these professionals received a three-day training by experts in the field focusing on sleep-promoting behavior, healthy eating behavior, screen time (addiction), and motivational interviewing.

The lifestyle intervention consists of a 12-week program (see Table 1) where the child and parents are treated intensively (approximately two hours a week). The intervention will start with psychoeducation sessions on a healthy lifestyle. In addition to providing more information about a healthy lifestyle, psychological treatment is necessary to achieve and maintain behavioral change. CBT has great evidence as an effective intervention method for behavioral change in mental health problems in adults and children (e.g., sleeping problems and eating disorders) [22]. Due to the amount of evidence of CBT, and the focus on both cognitions and behavior in lifestyle behavior, this psychological treatment was chosen for this intervention. A workbook is available for the child and the parents and contains information about a healthy lifestyle and describes the various assignments in detail. See Table 1 for a more detailed description of the content of the sessions. While the order of the sessions is the guideline of the intervention, a certain degree of flexibility is needed to fit the family's needs.

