These CBT sessions will be combined with PMST sessions for children and their parents. Because of this combination, children and parents can use the behavioral skills they have learned during CBT (e.g., behavioral experiments; using helpful thoughts) in assignments of the PMST. In this way, parents and children will get concrete examples of applying the learned CBT techniques. In PMST, children and their caregivers both learn skills (i.e., action-oriented approach) but also experience and get more knowledge about emotion regulation and how it feels in your body (i.e., experience-oriented approach) [16]. Furthermore, systemic interaction patterns between family members are quickly established. The PMST sessions will be held in the gymnasium.

In addition to the CBT and PMST sessions on location, there will be weekly visits by a home coach since family support at home is crucial for the child. The home coach will visit families in their homes each week to promote healthy behavior and help families apply new lifestyle skills. This home coach may also visit schools and sports clubs with the child to involve (and, if necessary, educate) teachers and trainers. The coach plays a crucial role in creating a healthy eating, exercise, and sleep environment in the family as well as setting boundaries and focusing on self-empowering the system. Targeting a child’s whole system and social context will promote lasting behavioral changes and family satisfaction. The home coach will discuss personal goals continuously with the children and their caregivers. The step from ‘no change’ to ‘some change’ is the most crucial. Targeting the family will stimulate the child and promote lasting behavioral changes.

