### Outcomes

Outcome parameters and measurement times are assessed as shown in Table 2.

**Table 2 Tab2:** Outcome parameters from baseline to 12 months after baseline

Measurement	T0^a^	T1^b^	T2^c^	T3^d^	Instrument
*Descriptives*					
A. Descriptives	T0				Intake questionnaire
B. Psychiatric evaluation	T0				DSM-V
C. Intelligence quotient (IQ)	T0				WISC-V
*Primary outcome*					
D. Quality of life	T0	T1	T2	T3	Kidscreen-27
*Secondary outcomes*					
E. Emotional and behavior problems	T0	T1	T2	T3	CBCL
F. Cognitive performance	T0	T1			COTAPP
G. Somatic measurements	T0	T1		T3	Somatic screening
H. Blood laboratory tests	T0				Blood samples (15 ml) sober
*Lifestyle parameters*					
I. Sleep: Sleeping habits	T0	T1	T2	T3	CSHQ
J. Sleep: Sleeping dairy	T0	T1	T2	T3	Sleep–wake diary
K. Sleep: 24 h sleep/wake measurements	T0	T1	T2	T3	Actigraphy
L. Diet: Food consumption	T0	T1	T2	T3	Nutrition diary
M. Diet: Eating habits	T0	T1	T2	T3	Eating habits questionnaire
N. Physical activity: Physical fitness	T0	T1		T3	Shuttle run test
O. Physical activity: Physical activity	T0	T1	T2	T3	Physical activity questionnaire
K. Physical activity: Actigraphy	T0	T1	T2	T3	Actigraphy
P. Screen time: Screen activities	T0	T1	T2	T3	Screen time questionnaire
*Measurements of costs*					
Q. Used healthcare resources				T3	Tic-P questionnaire
*Other study parameters*					
R. Parenting styles	T0	T1	T2	T3	VSOG
S. Parenting functioning	T0	T1	T2	T3	VGFO
T. Prior beliefs	T0				5-item questionnaire
U. Patient satisfaction			T2	T3	GGZ-Jeugdthermometer

*DSM* Diagnostic and Statistical Manual of Mental Disorders, *WISC* Wechsler Intelligence Scale for Children, *IQ* Intelligence quotient, *CBCL* Child Behavior Checklist (6–18), *CSHQ* Children’s sleep habit questionnaire, *Tic-P* Trimbos and iMTA questionnaire on Cost associated with Psychiatric illness, *VSOG* Verkorte Schaal voor Ouderlijk Gedrag, *VGFO* Vragenlijst Gezinsfunctioneren Ouders

^a^T0 Baseline

^b^T1 twelve weeks after baseline

^c^T2 six months after baseline

^d^T3 twelve months after baseline

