#### Secondary study parameter(s)

Concerning secondary outcome measurements, repeated measures techniques based on the intention-to-treat principle will be used to analyze the difference between the lifestyle intervention and the CAU group.

To get more insight into the prior beliefs of parents about short-term and long-term success, the outcomes of the 5-item questionnaire will be analyzed using the independent samples *t*-test to compare the lifestyle intervention group with the CAU group. Patient satisfaction and compliance with the intervention will be measured using the satisfaction measurement scale. The outcomes will be evaluated with a repeated-measures design.

The cost-effectiveness of the lifestyle intervention is measured with the TiC-P questionnaire. To assess this outcome, we will use an independent sample *t*-test to compare the lifestyle intervention with the CAU.

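### The cost-effectiveness aim rests on a t-test of one questionnaire at 12 months, whose recall misses the programme and months 0–9 of care, and no effect measure enters

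*Protocol article*

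**What the plan says.** The Background of the protocol article sets the aim: "the third aim is to investigate the cost-effectiveness of the lifestyle intervention compared with CAU". It also gives the expected direction: "We assume that intervening in lifestyle at such a young age will result in less expensive care in the long term".

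The cost instrument is the TiC-P. In Table 2 (Outcomes), the row "Q. Used healthcare resources" is marked at T3 only. The text under Measurements of costs agrees: "The number of all healthcare contacts with a 3-month recall period is registered at T3 (12 months after baseline". That section adds that the TiC-P also covers parents' productivity losses, and that the comparison with CAU is calculated from these data.

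The section Secondary study parameter(s) repeats the source, "The cost-effectiveness of the lifestyle intervention is measured with the TiC-P questionnaire", and fixes the method: "To assess this outcome, we will use an independent sample" t-test between the two arms.

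The section Lifestyle intervention describes a 12-week programme in which child and parents "are treated intensively (approximately two hours a week"), and says that in addition "there will be weekly visits by a home coach". The section Care as usual describes one 1.5-hour session for parents and an e-health module of about two hours for the child, followed by usual care.

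**The concern.** Two features of the stated plan do not fit the aim.

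- **The window.** Costs are asked about once, at the end, with short recall. The resources that distinguish the arms most clearly, namely the sessions and home visits, are spent early.
- **The analysis.** A cost-effectiveness result relates a difference in cost to a difference in effect. A two-sample t-test on TiC-P data does not do this. KIDSCREEN-27 is collected at all four assessments, but nothing in the article links it to cost.

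At stake is the reading of the third aim. If late care use turned out lower in the intervention arm, that could be reported as cost-effectiveness although the investment meant to produce it was not in the comparison. The programme is labour-intensive and the Discussion looks ahead to its use in practice, so such a statement would carry weight.

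**Working it through.** The article gives no figure to reproduce here. The check is a timeline followed by a comparison of what is estimated with what is needed.

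**Inputs**
- T3 is 12 months after baseline, taken as 52 weeks (Table 2).
- Recall for healthcare contacts is 3 months, taken as 13 weeks (Measurements of costs).
- The programme lasts 12 weeks at about 2 hours a week, plus weekly home visits (Lifestyle intervention).
- T0 is planned three weeks before treatment starts (Procedures).
- CAU input is 1.5 hours for parents and about 2 hours of e-health for the child (Care as usual).

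**Step 1: the recall window.** Start = 52 − 13 = week 39; end = week 52. Share of follow-up = 13/52 = 25%. The other 39 weeks, or 75%, are not asked about.

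**Step 2: overlap with the programme.** Overlap = max(0, min(programme end, 52) − max(programme start, 39)).

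| Programme timing | Weeks | Overlap | Gap to window |
|---|---|---|---|
| Starts at T0 | 0–12 | max(0, 12 − 39) = 0 | 39 − 12 = 27 weeks |
| Starts 3 weeks after T0 | 3–15 | max(0, 15 − 39) = 0 | 39 − 15 = 24 weeks |

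The overlap is zero on either reading, and the gap is too wide for modest delays to matter.

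**Step 3: what lies outside the window.** In the intervention arm: 12 × 2 = 24 hours of sessions and about 12 home visits per family, if visits run through all 12 weeks. In the CAU arm: 1.5 + 2 = 3.5 hours of psycho-education, assuming it is given early. In both arms: every other healthcare contact in months 0–9.

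**Step 4: what the t-test estimates.** Write the 12-month cost difference (intervention minus CAU) as

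ΔC = ΔC(delivery) + ΔC(other care, months 0–9) + ΔC(months 9–12).

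The test addresses only the last term. It omits ΔC(delivery) + ΔC(other care, months 0–9).
- The delivery term should be positive, since 24 staffed hours plus home visits face one 1.5-hour session and an e-health module. Dropping it favours the intervention.
- The sign of the other-care term is unknown. The section Participants bars intervention families from starting other treatment during the 12 weeks, apart from medication optimisation, and states no such bar for CAU. CAU families may therefore use more other care in the uncounted months.

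The sign of the sum cannot be determined from the article.

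**Step 5: the effect side.** A cost-effectiveness statement needs ΔC together with ΔE. No ΔE appears in the stated analysis.

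**The case against.** The strongest reply is that this is a journal article. Unit costing of a scheduled programme needs no parent questionnaire and could be done from delivery records. Costing methods, incremental ratios and bootstrap details commonly sit in a full protocol or economic plan that is not shown. Part of this stands: a reader might infer that programme cost will never be counted, and the article does not establish that. It does not answer the point, however. The article states timing, data source and test, and three places agree on them. It says that the result is calculated from the T3 data. The stated rule does not deliver the aim.

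A reader might also infer that the whole comparison is biased towards the intervention. The article supports this only for delivery cost. CAU families' other care in months 0–9 is uncounted too, so the net direction is open.

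Nor does the 25% apply to everything the TiC-P measures. The three-month recall is stated for healthcare contacts; none is given for productivity losses.

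Finally, late-period costs are not worthless. They bear on the article's own expectation about long-term care costs, and the primary outcome and the other secondary outcomes do not depend on this analysis. That lowers the severity but does not remove the mismatch.

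**Conclusion.** The concern holds in this form. As written, the plan produces a between-arm comparison of late resource use or cost and not a cost-effectiveness result. Healthcare contacts are observed for 3 of 12 months. The programme has zero overlap with that window, ending 24 to 27 weeks before it opens. No effect measure is included.

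This rests on T3 being close to week 52, on the programme starting within about three weeks of baseline, and on the T3 TiC-P being the only cost source, as the article says. The amount and net direction of the omitted costs cannot be calculated from the article, which gives no unit costs and no data on care use in months 0–9.

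This should be fixed before the third aim is analysed or reported. It does not threaten the primary comparison.

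**What to change.** 1. **Delivery cost.** Cost the sessions and home visits actually delivered, and the CAU psycho-education, per child from delivery records. Add these costs to both arms.
2. **Months 0–9.** Obtain healthcare use for every child from care records. Where children are still in follow-up, add the TiC-P at T1 and T2. With three-month recall this would cover roughly months 0–3 and 3–6, so with T3 about 9 of 12 months (75%); months 6–9 would still need records or a longer recall at T3. State that institutional records miss care received elsewhere and productivity losses.
3. **Analysis.** Replace the t-test as the cost-effectiveness analysis. Estimate incremental cost and incremental effect jointly, with a bootstrap interval. Name one KIDSCREEN-27 dimension or score in advance as the effect, because the section Primary outcome defines five dimension scores and no total.
4. **Fallback.** If months 0–9 cannot be recovered, restate the aim and conclusion as a comparison of healthcare use and costs in months 9–12, and make no cost-effectiveness claim.

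The first three cost some record extraction and analysis work, and slightly more parent burden if the questionnaire is added. With follow-up expected to end in early 2025, added questionnaires may reach few children, so the record-based steps matter most. The fallback costs only a narrower aim.

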#### Other study parameters

R. Parenting stylesParenting styles are examined using the Brief Scale of Parental Behavior (25 items) (BSBP: English translation of ‘Verkorte Schaal voor Ouderlijk Gedrag (VSOG)’) [48] at T0 (Baseline). This questionnaire is used to assess potential changes in pedagogical style during the intervention. The Brief Scale of Parental Behavior has a 5-point scale that ranges from 1 (*(almost) never*) to 5 (*(almost) always*) [48]. A low score on two subscales indicate inadequate parenting styles, while a high score on the three remaining subscales indicates inadequate parenting styles [48].S. Parenting functioningTo assess changes in family functioning during treatment, the Family Functioning Questionnaire (28 items) (FFQ: English translation of ‘Vragenlijst Gezinsfunctioneren Ouders (VGFO)’) [49] is used at T0 (Baseline). The FFQ has a 4-point scale ranging from 1 (*not applicable*) to 4 (*completely applicable*), with lower scores suggesting more problems with family functioning [49].T. Prior beliefsTo evaluate parents’ previous beliefs on the short-term and long-term efficacy and challenges of the lifestyle intervention, a 5-point scale questionnaire from 0 (*completely disagree*) to 5 (*completely agree*) is used. Prior beliefs are measured at T0 (baseline).U. Patient satisfactionPatient satisfaction and treatment compliance are measured using the GGZ-Jeugdthermometer [50]. This instrument permits institutions to overlook how clients and parents of clients appreciate the care provided. Parents assess their satisfaction with the information they received about the treatment, the team of psychologists, the amount of shared decision-making, and the results of the treatment. Furthermore, parents value their children's experiences during treatment and of their own. Finally, parents can rate their overall experience on a scale of 0 to 10. Patient satisfaction will be measured at T3 (12 months after baseline).

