#### Care as usual

Care as usual (CAU) consists of a 1.5 h-session of psycho-education on healthy lifestyle for the parents only. This psycho-education consult is given by a psychologist which is trained for this research. The children have to follow an e-health psycho-education module about healthy lifestyle on a device of their choice (e.g., a mobile phone, laptop, or tablet), which will take them about two hours (in total) to complete. However, this module does not have to be taken through in one go. As well as for the psycho-education consult of parents as for the e-health module of the children, the content consist of information on healthy eating behavior, healthy use of screen time, healthy sleep patterns, and physical exercise. A conscious decision was made to include psycho-education about a healthy lifestyle in the control condition. We decided to offer parents and children in the CAU group a psycho-education session on healthy living and access to the e-health psycho-education module in exchange for the information we gather during assessments. After this, the child and family will receive care as usual (e.g., optimization of pharmacotherapy).

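### Treatment compliance is assigned to a parent satisfaction scale, so the adherence outcome would report satisfaction rather than participation

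*Protocol article*

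**What the plan says.** The Abstract's list of secondary outcomes has adherence and satisfaction as two separate items. The aims at the end of the Background add that "this study aims to identify potential moderators of adherence or responders to the treatment", with socioeconomic status, ethnicity and comorbidity as examples.

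One instrument is then given to both constructs. Item U under Other study parameters says that patient satisfaction and "treatment compliance are measured using the GGZ-Jeugdthermometer". The statistical section on secondary parameters agrees: "Patient satisfaction and compliance with the intervention will be measured using the satisfaction measurement scale". It adds that the results will be evaluated with a repeated-measures design.

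Item U gives the purpose of the scale: "This instrument permits institutions to overlook how clients and parents of clients appreciate the care provided". On content it says "Parents assess their satisfaction with the information they received about the treatment, the team of psychologists, the amount of shared decision-making", and goes on to the results of treatment, the experiences of child and parents, and an overall rating from 0 to 10. On timing it says "Patient satisfaction will be measured at T3 (12 months after baseline", whereas row U of Table 2 marks both T2 and T3.

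The intervention is a 12-week programme with 12 sessions in Table 1, at about two hours a week. In addition, "The home coach will visit families in their homes each week". The control arm gets a 1.5-hour session for parents and an e-health module of about two hours for the child, done at the family's own pace: "However, this module does not have to be taken through in one go".

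**The concern.** Whether a family took part and whether it was pleased with the care are different things, and the Abstract treats them as different. A family can value the team and stop early, or attend throughout and be disappointed with the result. A scale of appreciation cannot tell these families apart by participation.

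An adherence result taken from this scale would be a satisfaction result under another name, and its moderators would be predictors of satisfaction. This matters in this trial because the programme is intensive, the order of sessions may be adapted to the family, and the Discussion itself expects that the load may cause dropouts. Readers will want to know how much of the programme was received, and the measure named for that purpose does not say.

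**Working it through.** No sample size, power or error rate is involved. The check compares the stated construct with the stated measure, and then looks for another source in the article.

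**1. Construct against content.**

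| What participation would consist of | Planned amount | Counted in the scale as described |
|---|---|---|
| On-site sessions (Table 1) | 12 | No |
| Home-coach visits, weekly for 12 weeks | 12 × 1 = about 12 | No |
| Control arm: parent session | 1 | No |
| Control arm: child e-health module | 1 | No |

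Intervention contacts: 12 + 12 = about 24. Control components: 1 + 1 = 2. The described content counts none of them. The 24 is approximate; session 8, for example, also includes a separate parent contact for video feedback.

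**2. Timing of the scale.** Table 2 puts T1 twelve weeks after baseline, while Procedures puts T0 three weeks before treatment starts. Counted from T0, a 12-week programme therefore ends at week 12 or at week 3 + 12 = 15. T2 is at week 26 (six months; the sample size section also uses 26 weeks), and T3 is at about week 52.

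- Gap to T2: 26 − 15 = 11 weeks to 26 − 12 = 14 weeks.
- Gap to T3: 52 − 15 = 37 weeks to 52 − 12 = 40 weeks.

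If item U is right (T3 only), the first reading comes 37 to 40 weeks after the programme ends. If Table 2 is right, it comes after 11 to 14 weeks. Under neither reading is the scale given at T1.

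**3. Who supplies it.** Only families still answering at T2 or T3 do. The sample size section allows for 20% dropout, which is 0.20 × 80 = 16 children. If dropout reached that level and those families did not return the scale, up to 16 of 80 would have no compliance value. Families who stopped the programme may well be over-represented among them.

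**4. Other possible sources in the article.**

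- Table 2 has no row for adherence, attendance or fidelity.
- The Tic-P counts healthcare contacts, but with a 3-month recall at T3. That covers about weeks 39 to 52 (52 − 13 = 39), starting at least 39 − 15 = 24 weeks after the programme has ended.
- The interviews cover facilitators, barriers and implementation, but only in an intervention-arm subsample recruited to saturation and the professionals involved. They give no count per family.

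**5. Analysis against timing.** A repeated-measures evaluation needs at least two readings. Table 2 provides two (T2 and T3); item U provides one. The three statements cannot all stand.

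**The case against.** The strongest reply is that the article defines neither compliance nor adherence, so reading them as participation is an interpretation. The scale's items are in a cited source that is not at hand, and one of them might concern completing treatment. A journal article may also leave attendance records to the full protocol, so their absence here does not show that none are kept.

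Much of this is fair. The judgement rests on the article's own summary of the scale, and attendance data may exist. But the point is not that a detail is missing. The article names an instrument for compliance in two places, and by its own description that instrument measures appreciation of care. Participation is also the ordinary meaning of adherence once it is listed apart from satisfaction.

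Some stronger readings are tempting, and the article does not support them:

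- **The whole moderator aim is lost.** The aim covers adherence or responders, and responders can be studied with the outcome scales.
- **A null primary result could not be interpreted.** The primary comparison follows intention to treat and does not use adherence, and the interviews give some information on delivery.
- **Families would be misclassified as compliant or non-compliant.** The article sets no such rule or cut-off.
- **The link between adherence and quality of life would be circular because the scale includes perceived results.** The article plans no such analysis.
- **Content varies freely between families.** Goals and focus are tailored, but the Lifestyle intervention section says the techniques, structure and working elements are the same for all.

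**Conclusion.** The concern holds for the measurement of adherence and goes no further. The stated measure does not fit the stated construct: its described content covers none of the roughly 24 intervention contacts or the two control components, and its first reading comes 11 to 14 weeks (Table 2) or 37 to 40 weeks (item U) after the programme. Followed as written, the plan would report satisfaction as adherence, and moderators of satisfaction as moderators of adherence. The timing of the scale is also inconsistent between Table 2, item U and the planned repeated-measures evaluation.

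This should be corrected, but it does not threaten the primary result or any efficacy conclusion. The conclusion assumes that adherence means taking part in the planned sessions, visits and module, and that the article's summary represents the scale's content. A reader might infer that the trial holds no data on participation at all; the article does not show that, only that it names no such data as the compliance measure.

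**What to change.** In item U and in the statistical section on secondary parameters, define compliance as participation:

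- intervention arm: number of Table 1 sessions attended and number of home-coach visits received;
- control arm: parent session attended (yes or no) and e-health module completed.

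Take these from clinic appointment records and module usage data where they exist. That they exist is an assumption, because the article mentions neither. By the article's own schedule, data collection was to finish in spring 2024 and follow-up at the beginning of 2025. If collection is complete, extract the counts retrospectively and report how many families have them.

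Use the counts for the adherence outcome and for its moderators. Keep the GGZ-Jeugdthermometer for satisfaction only. State one schedule for it in Table 2 and item U, and match the analysis: repeated measures if it is given at T2 and T3, a single-time comparison if at T3 only.

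The cost is a little extra data extraction and entry. No additional visits or questionnaires are needed.
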